**Fig. 2 Fig2:**
[figure not shown]
Healthcare pathways for PDOC. EIN: Early intensive neurorehabilitation –duration max 14 weeks. PIN: Prolonged intensive neurorehabilitation –up to 2 years post injury

**Fig. 3 Fig3:**
[figure not shown]
Measurement plan

### Data collection

In 4 years we aim to include 72 patients. Structured data collection (Fig. 3) will take place at the start of the EIN programme at week 5, 10, and at EIN discharge (week 14). LOC assessment and registration of complications will be done weekly.

After discharge from EIN, follow-up measurements are planned at 28, 40, 52, and 104 weeks post-inclusion. These will take place at the patients’ actual health-care institution or residence.

All measurements conducted during the EIN programme are performed by trained members of the rehabilitation team. Follow-up measurements are performed by a trained research assistant.

### Complications

The number and type of complications is classified according to the International Classification of Functioning, Disability and Health (ICF) in the domain of functions and structures (Table 2). In addition, the number of imaging studies and types of treatments for complications (surgery, non-surgery, ICU transfers, procedures i.e.) are recorded.

**Table 2 Tab2:** Classification of complications

• Mental/nervous system	
o Epilepsy	
o Hydrocephalus	
o Paroxysmal Sympathetic Hyperactivity (PSH)	
o Disturbed sleep/wake cycles	
• Sensory systems	
• Cardiovascular, haematologic, immunologic and respiratory systems	
o Thromboembolic disease	
o Abnormal laboratory findings (e.g. hyponatremia)	
• Digestive, metabolic and endocrine systems	
o Gastro-intestinal: vomiting, diarrhoea, obstipation	
• Genitourinary and reproductive systems	
• Musculoskeletal and movement-related systems	
o Contractures measured by joint range of motion (ROM)	
o Spasticity: Modified Ashworth scale	
o Heterotopic ossification	
• Skin and related structures	
o Skin breakdown: EPUAP stages I-IV (Dutch guideline: pressure ulcer: prevention and treatment [27]	
• Infection	
Body system	
o Respiratory	
o Urinary tract	
o Blood	
o Stool	
o CSF, brain	
o Wound/skin	
o Ear/eye	
Antibiotic-resistant bacteria	

### Mortality

We will register the following causes of death: [28].
Death from (co) morbidity despite treatmentDeath from comorbidity after a non-treatment decision (non-resuscitation or withholding treatment for medical complications)Death after withdrawal of artificial nutrition and hydration.

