**Methods:**

Single-centre prospective cohort study with a 2-year follow-up period. Patients with PDOC due to acute brain injury who receive EIN, aged 16 years and older are included. Measurements will take place at start EIN, in week 5, 10, and at discharge from the EIN programme (duration = max 14 weeks) and at week 28, 40, 52, and 104 after admission to the EIN programme, following patients through the health-care chain. Outcome measures are the changes over time in level of consciousness, using the Coma Recovery Scale-Revised; the frequency and type of medical complications; the mortality rate; level of disability, including the level of motor, cognitive, behavioural and emotional functioning; participation; and quality of life. Secondary outcomes include self-efficacy of caregivers, caregivers’ strain and cost-effectiveness of the programme.

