Research on recovery shows that 38 and 78% of patients with PDOC due to traumatic brain injury (TBI) regain (minimal) consciousness at respectively 3 and 12 months post injury [2]. In patients with non-traumatic brain injury (NTBI) only 17% regains consciousness at 8 months post injury [2]. Aidinoff et al. [14] demonstrated an improvement in survival and recovery of consciousness in UWS patients over the last two decades after EIN, and similar outcomes for both TBI and NTBI UWS. These outcomes suggest that improvements in acute medical care and EIN have contributed to advances in UWS care. Treatment started within 8 weeks after injury is associated with better outcomes in terms of LOC and functioning, gained in a faster pace than treatment started after 8 weeks [15–17]. In patients with PDOC of mixed aetiology with a mean time follow-up of 5 years, 40% of survivors reached functional independence, while 42% of patients able to respond to a self-report questionnaire, reported a poor quality of life [18]. The EIN programme in the Netherlands has been studied before; in patients aged < 25 years recovery of consciousness occurred in two-thirds at the end of the EIN programme [19] and two-thirds of the patients who were fully conscious at discharge were able to live independently after 10–12 years [20].

Prognostic factors associated with better recovery from PDOC are younger age at onset, traumatic aetiology, less severe comorbidities and less severe neurological impairment, i.e. higher level of consciousness at admission to EIN [2, 4, 15, 21–25]. However, most studies on recovery after PDOC suffer from methodological issues, such as a retrospective design [2] and variability in clinical decision making in acute care [2]. Further, research on outcomes after PDOC often fails to discriminate between diagnostic subtypes (UWS or MCS), aetiology and the time since injury [2]. Furthermore, data on quality of life, costs and cost-effectiveness of rehabilitation programmes, and caregiver burden are limited.

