### Statistical analysis

Descriptive statistics will be used to present the outcomes of the study parameters and the socio-demographic data. Means and standard deviations will be calculated for variables on an interval scale and medians and interquartile ranges for ordinal variables. Proportions will be calculated for nominal variables.

Subgroup analyses will be performed for patients presenting in UWS versus MCS at baseline and for traumatic versus non-traumatic disorders of consciousness.

The proportions of patients transitioning from UWS to MCS and emergence from MCS to the conscious state will be calculated during and after EIN.

The course of recovery of consciousness (yes/no) over time will be analysed using Generalized Estimating Equations (GEE) analysis for logistic outcomes on an intention-to-treat basis. Assuming that data are missing at random, data imputation is unnecessary in GEE analysis; all observations are taken into account in contrast to complete case analyses. Recovery (yes/no) at each time point will be included as the dependent variable in the GEE model. Separate models will be generated for transitions from UWS to MCS and from MCS to the fully conscious state based on the CRS-R. Independent variables that will be added one by one to the models, include- measurement time (weeks), traumatic vs. non-traumatic aetiology, age at injury, and complications (yes/no or number). Significant predictors (*p* < 0.05) will be included in a multivariable model using a Bonferonni correction, dividing the significance level (alpha< 0.05) by the number of predictors included in the model.

Also using GEE analysis, the course of quality of life (EQ-5D-5L and Qolibri) and participation (CIQ) over time will be analysed using separate linear outcome models. The effects of time, cognitive (MoCa), behavioural (NPI), emotional (HADS), and motor status (FIM), and level of disability (DRS) and discomfort (NCS) on quality of life or participation during follow-up will be studied by adding these time-dependent variables (one by one) as independent variables to the models. Significant predictors (*p* < 0.05) will be added into a multivariable GEE-model to study the independence of these potential predictors on the outcomes using the Bonferroni correction.

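### The recovery models give deaths after treatment-limiting decisions no stated role, so a factor linked only to those decisions can appear associated with recovery

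*Protocol article*

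**What the plan says.** The Mortality section of the protocol article registers cause of death in three categories. The first is death despite treatment. The second follows a non-treatment decision, explained as "non-resuscitation or withholding treatment for medical complications". The third is "Death after withdrawal of artificial nutrition and hydration". The abstract lists "the mortality rate" among the outcome measures.

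The Statistical analysis section fixes the recovery models: "Recovery (yes/no) at each time point will be included as the dependent variable in the GEE model". There are separate models for the transition from UWS to MCS and from MCS to full consciousness. The "Independent variables that will be added one by one to the models" are measurement time, traumatic versus non-traumatic aetiology, age at injury and complications. The section assumes data missing at random and concludes that GEE needs no imputation. It mentions no weights. Neither death nor its category appears as an outcome state, covariate, censoring rule or sensitivity analysis. The analysis is labelled intention-to-treat, but that does not say how a patient is coded after death.

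The Data collection section sets the size and the length of observation: "In 4 years we aim to include 72 patients", and "follow-up measurements are planned at 28, 40, 52, and 104 weeks post-inclusion".

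**The concern.** A patient who dies after treatment is limited has no later level of consciousness to observe. Such decisions are plausibly made mainly for patients who have not recovered, so leaving the data depends on the outcome already seen. GEE without weights is not generally valid in that situation: it generally needs missingness unrelated to the outcome given the covariates, which is stronger than missing at random. The stated rule therefore does not cover these deaths.

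Three candidate predictors are exposed. The Background lists younger age and traumatic aetiology as known favourable factors, so they may well influence decisions. Complications are tied to the second death category by its own definition. The Discussion says that the results should help benchmark the programme and improve prediction of outcome. A coefficient that partly records for whom treatment was limited would be misread in both uses.

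**Working it through.** The protocol gives no expected mortality, no withdrawal rate and no figure to reproduce. All rates below are assumptions that show the mechanism.

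**1. Single-endpoint illustration, factor with no true effect**

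Assumptions: in both groups 40% have recovered by week 28 and a further 10% would recover later, so 50% would recover if treatment were never limited. Treatment-limited death strikes a fraction q of the 60% unrecovered at week 28, regardless of whether they would have recovered later.

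- Deaths counted as non-recovery: P = 0.40 + 0.10(1 − q)
- Survivors only: P = [0.40 + 0.10(1 − q)] / (1 − 0.60q)

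| q | Deaths as non-recovery | Survivors only |
|---|---|---|
| 0.10 | 0.490 | 0.490/0.94 = 0.521 |
| 0.20 | 0.480 | 0.480/0.88 = 0.545 |
| 0.35 | 0.465 | 0.465/0.79 = 0.589 |

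Odds ratios against a group with q = 0.10:

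- Deaths as non-recovery: (0.480/0.520)/(0.490/0.510) = 0.96 for q = 0.20; (0.465/0.535)/(0.490/0.510) = 0.90 for q = 0.35.
- Survivors only: 1.10 for q = 0.20; 1.31 for q = 0.35.
- Unrecovered survivors at week 28 weighted by 1/(1 − q): recovered = 0.40 + 0.10(1 − q)/(1 − q) = 0.50 of a total of 0.40 + 0.60 = 1.00, in every group. The odds ratio is 1.0.

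The survivors-only result thus matches neither recovery under current care (0.96-0.90) nor recovery had treatment not been limited (1.0).

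**2. Week 104, deaths only among patients who would never recover**

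Latent recovery is 50% in both groups, and death proportions are d1 with and d0 without the factor. Observed recovery among survivors is 0.5/(1 − d), so OR = (0.5 − d0)/(0.5 − d1).

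- 10% v 5%: 0.45/0.40 = 1.13
- 18% v 2.5%: 0.475/0.32 = 1.48
- 30% v 5%: 0.45/0.20 = 2.25

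Counting these deaths as non-recovery gives 50% v 50%, an odds ratio of 1.0.

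**3. Simulated logistic GEE**

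The model has visits at weeks 5 to 104, terms for factor and time, an independence working correlation and robust standard errors. Latent recovery is 50% by week 104 in both halves. Deaths occur from week 14 in unrecovered patients only. Each scenario was run once with 20,000 patients; without any deaths the runs gave odds ratios of 0.96-1.03, which shows the simulation noise.

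| Deaths with v without factor | Would some of the dead have recovered? | OR, deaths drop out | OR, deaths as non-recovery | OR, same run without deaths |
|---|---|---|---|---|
| 26% v 4% | yes | 1.16 | 0.94 | 1.03 |
| 44% v 7% | yes | 1.19 | 0.82 | 0.97 |
| 18% v 2% | no | 1.13 | 0.98 | 0.98 |
| 30% v 5% | no | 1.28 | 0.99 | 0.99 |

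The GEE ratios are smaller than those in step 2 because early visits, with few deaths, enter the same coefficient.

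**4. Rejection at 0.05 with 72 patients** (1,300 simulated trials per scenario, Monte Carlo error about 1.2 to 1.6 points)

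| Deaths with v without factor | Deaths drop out | Deaths as non-recovery | No deaths |
|---|---|---|---|
| 26% v 4% | 6.2% | 5.6% | 5.5% |
| 44% v 7% | 6.8% | 5.4% | 5.2% |
| 30% v 5% | 9.9% | 6.1% | 6.1% |

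**The case against.** The strongest objection is that this is a condensed article, that sensitivity analyses belong in an analysis plan not shown, and that recording these deaths separately is good practice. The last part is right. The first does not dispose of the point, because the article itself fixes the model, the predictor list and the missing-at-random, no-imputation rule, and that rule is what fails for these deaths.

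A second objection is that the study describes recovery under current Dutch care, so prognosis that includes treatment decisions is a legitimate target. That stands. It supports counting deaths as non-recovery for that purpose, but not letting them drop out, which answers neither question.

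Third, the rates are assumed, and the excess of false positives at 72 patients is small. The Bonferroni threshold in the multivariable model is stricter still. This stands and limits the claim.

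Three stronger readings are tempting and are not supported:

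- A reader might infer a self-fulfilling prophecy, in which factors believed unfavourable are confirmed as such. That direction arises only if deaths count as non-recovery and some of those who died would have recovered. On the most natural reading of the plan, deaths drop out and the factor looks favourable, or a truly adverse effect is diluted.
- A reader might infer that the decisions alone set the direction. In the illustration, identical decisions give odds ratios on either side of 1 according to how deaths are handled.
- A reader might see the Background as condemning the study's own practice. Its criticism of earlier studies is of "variability in clinical decision making in acute care", whereas patients enter DOCTOR after acute care. It makes the mechanism plausible but is no self-contradiction.

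**Conclusion.** The concern holds as something that can happen, not as something that will. The plan registers two categories of treatment-limited death, then models recovery under a missing-data rule that does not cover them. Under the assumed 10% v 20-35% death rates among unrecovered patients, a null factor has an odds ratio of 1.10-1.31 if deaths drop out and 0.96-0.90 if they count as non-recovery. In the simulated GEE the ranges are 1.13-1.28 and 0.99-0.82, with about 1.0 in the latter case when none of those who died would have recovered.

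The conclusion rests on two assumptions: that these deaths fall mainly on unrecovered patients, and that their frequency differs by predictor. The protocol gives no data on either. At 72 patients the rejection rate rises from about 5-6% to 6-10% at most, so the main loss is in interpreting the estimates for age, aetiology and complications. The change should be made, but the point does not invalidate the study.

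**What to change.** Before the data are analysed:

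1. State how deaths enter the main GEE in each of the two transition models.
2. Tabulate treatment-limited deaths (second and third categories) by each candidate predictor.
3. Report beside the main GEE, with confidence intervals, two sensitivity analyses: (a) deaths counted as not recovered, which addresses recovery under current care; and (b) censoring at treatment-limited death, with inverse-probability weights from a small set of variables that includes the last level of consciousness, which addresses recovery had treatment not been limited.
4. Report predictors whose estimates change materially between these analyses as sensitive to treatment-limiting decisions.

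Agreement in direction between (a) and (b) should not be a condition for calling a factor a predictor. It is no test, and a noisy weighted estimate could veto a real predictor.

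The cost is analysis time only, since causes of death are already registered. The weights will be imprecise if deaths are few, and (b) assumes that the chosen variables capture what drives the decisions, so both analyses remain supportive.

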### Measurement instruments

#### Coma recovery scale revised (CRS-R)

The CRS-R [29] is a bedside assessment tool for differentiating levels of consciousness by observation of responses to various stimuli. It is composed of 6 hierarchical subscales: auditory, visual, motor, oromotor/verbal, communication and arousal with 23 dichotomously scored items [30]. The item content of the CRS-R identifies ascending levels of conscious behaviour/ability and using a combination of items to differentiate UWS from MCS from emerged from an MCS based on The Multi-Society Task Force on Persistent Vegetative State and Aspen Workgroup criteria [29]. An American Congress of Rehabilitation Medicine practice parameter recommends the use of the CRS-R based on its standardised administration and scoring procedures, item content, and inter-rater and test-retest reliability [26, 29].

#### Nociception coma scale (NCS)

The NCS is a nociception behaviour observation tool, developed for patients with PDOC [31]. It includes four subscales assessing motor, verbal, visual and facial responses; each subscore ranges from 0 to 3 (total score: 0–12). A higher total score indicates a higher level of possible discomfort and pain [32].

#### Disability rating scale (DRS)

The DRS is an observational measurement of the levels of arousal, awareness, and responsiveness (including eye opening, communication ability, and motor response); cognitive ability of self-care activities (such as feeding, using the toilet, and grooming); dependency on others (level of functionality); and psychosocial adaptability (employability). The DRS score ranges from 0 to 29 (low to high level disability) and scores are categorised into the following disability categories: 0 = none, 1 = mild, 2–3 = partial, 4–6 = moderate, 7–11 = moderately severe, 12–16 = severe, 17–21 = extremely severe, 22–24 = vegetative state, and 25–29 = extreme vegetative state. The DRS has been used as an outcome measure in multiple previous studies on PDOC outcome [13, 15, 17, 19].

#### Functional Independence measure (FIM)

The FIM measures the level of a patient’s disability and indicates how much assistance is required for conducting activities of daily living [33]. The FIM contains 18 items composed of 13 motor tasks and 5 cognitive tasks. Tasks are rated on a 7-point scale, ranging from 1 = total assistance to 7 = complete independence. FIM total scores range from 18 to 126, with higher scores reflecting a higher level of functioning [34].

#### Community integration questionnaire (CIQ)

The CIQ is a 15-item questionnaire that assesses participation in 3 domains: within the home environment, in social interactions, and in productive activities (work, school, or volunteering) [35]. The basis for scoring is primarily the frequency of performing activities or roles, with secondary weight given to whether activities are done jointly with others, and the nature of these other persons (for example, with/without TBI). CIQ scores range from 0 to 29, a higher total score indicates a higher level of participation.

#### EuroQuol-5D-5L (EQ-5D-5L)

Health-related quality of life is measured using the EQ-5D-5L [36, 37]. It consists of a 5-item EQ-5D index (mobility, self-care, usual activities, pain/dis- comfort and anxiety/depression) and a visual analogue scale (EQ-VAS). Psychometric properties of the Dutch version are shown to be good. The five EQ-5D index items are summarised into one weighted overall score, which runs from 0 for the value of death to 1.00 for full health. The EQ-VAS ranges from 0 to 100 (worst to best imaginable health state). For the general Dutch population average EQ-5D index = 0.843 and average EQ-VAS = 81.36 [37]. At the start of the study, the questionnaire will be completed only by proxy, as soon as the patient regains consciousness, the questionnaire will be filled in both by proxy and patient.

#### Quality of life in brain injury (QOLIBRI)

The QOLIBRI was developed by an international task force in two multi-language studies involving more than 2000 persons after traumatic brain injury (TBI) [38]. The QOLIBRI is a comprehensive questionnaire with 37 items covering six dimensions of disease-specific health-related quality of life (HRQoL). The questionnaire provides a profile of quality of life together with a total score. The QOLIBRI scores are reported on a 0–100 scale, where 0 is the worst possible quality of life and 100 the best possible quality of life.

#### Hospital anxiety and depression scale (HADS)

The Dutch Hospital Anxiety and Depression Scale is used as a general measure of emotional distress and contains two subscales: anxiety and depression [39]. Subscale scores ≥8 might indicate the presence of a depressive disorder or an anxiety disorder. Reliability and validity are adequate for several clinical populations, including multiple sclerosis and acquired brain injury [40, 41].

#### The Montreal cognitive assessment (MoCA)

The MoCA is designed as a rapid screening instrument for cognitive dysfunction [42]. It assesses different cognitive domains: attention and concentration, executive functions, memory, language, visioconstructional skills, conceptual thinking, calculations, and orientation. The total possible score is 30 points; a score of ≥26 is considered as normal, 18–25 indicates mild cognitive impairment, 10–17 moderate cognitive impairment and < 10 severe cognitive impairment.

#### Neuropsychiatric inventory (NPI)

The Neuropsychiatric Inventory (NPI) is designed to be a retrospective (last month) interview assessing neuropsychiatric symptoms conducted with informants about patients for whom they care. The NPI consists of 12 domains, with each domain reflecting a cardinal neuropsychiatric symptom. The NPI provides symptom frequency, severity and distress ratings for each symptom reported, and total severity and frequency scores reflecting the sum of individual domain scores (range 0–144). A higher total score indicates a higher number of neuropsychiatric symptoms [43, 44].

#### Self-efficacy of caregiver (GSES)

Partners’ general self-efficacy is measured using the General Self-efficacy scale (GSES) [45]. This self-assessment scale contains 10 items scored on a 4-point scale ranging from ‘completely incorrect’ to ‘completely correct’. By adding all item scores, a total score is obtained with higher scores indicating greater self-efficacy.

#### Caregiver strain index (CSI)

The CSI assesses informal caregiver’s burden. The CSI contains 13 items. Scores range from 0 to 13, with higher scores indicating higher burden [46].

#### Trimbos and iMTA questionnaire on costs associated with psychiatric illness (TiC-P)

The TiC-P will be used to collect data on healthcare use from both a healthcare and societal perspective during follow-up. This questionnaire consists of two parts. The first part consists of questions on the number of consultations with healthcare providers during the previous 2 months. These include outpatient visits, hospital admissions, day care, etc. Also, the frequency and dosage of medication use is recorded. The second part of the TiC-P includes the Short Form of the Health and Labour Questionnaire (SF-HLQ), which involves questions on absence from and return to paid or voluntary employment for measuring productivity losses [47].

